### Sample size calculation

Several studies have investigated the therapeutic efficacies of PDE5 inhibitors (the majority employed sildenafil as a study drug) in patients with chronic SHF [10,22]. Most clinical trials have adopted maximal V_O2_ to calculate the sample size and statistical power. In a study of 34 patients with SHF and pulmonary hypertension, Lewis and colleagues reported a 14% increase in maximal V_O2_ by sildenafil administration (from 12.2 ± 0.7 to 13.9 ± 1.0 ml/g/minute) [10]. On the other hand, in a study investigating the efficacy of sildenafil in 23 patients with SHF, Guazzi and colleagues reported an increase in maximal V_O2_ of approximately 21% (from 12.9 ± 6.8 to 15.6 ± 6.0 ml/minute/kg) [22].

Assuming a mean baseline maximal V_O2_ of 14.0 ml/kg/minute, a percentage increase in maximal V_O2_ of 0% in the placebo group and 15% in the udenafil group (data taken from the study by Lewis and colleagues [10] and our previous experiences), we anticipate final maximal V_O2_ values of 14.0 ml/kg/minute in the placebo group and of 16.1 ml/kg/minute in the udenafil group, with a conservative standard deviation for mean maximal V_O2_ of 2.5 ml/kg/minute. Accordingly, we calculated the sample size assuming a standard deviation of 2.5 ml/kg/minute using the following formula:

$$n_{i}=\frac{2{\left(Z_{a/2}+Z_{\beta }\right)}^{2}\sigma^{2}}{{\left(\mu_{1}-\mu_{2}\right)}^{2}}$$

Based on these assumptions and calculations, detection of the 15% increase in maximal V_O2_ by udenafil, with a power of 80% and a statistical significance level of 5%, will require 23 patients per group for a standard deviation of 2.5 ml/kg/minute. Thus, allowing for a loss of 10% (data are missing completely at random, which implies that the missing data are unrelated to the study variables), a maximum of 52 patients would be required or 26 patients per group.

### Statistical considerations

The principal analysis will be conducted on an intention-to-treat basis. We will analyze all patients according to the randomization scheme. However, data that are missing completely at random will be omitted without analysis. The differences between the treatment groups in the main outcome will be assessed using an unpaired *t* test adjusted by baseline values (analysis of covariance). Binary endpoints will be compared using Fisher’s exact probability test. For survival analysis and clinical events, Kaplan–Meier survival curves will be plotted and compared using the log-rank test based on a proportional hazards model using the chi-square test. Statistical significance will be accepted for *P* <0.05.

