### Study design and medications

Patient screening for trial eligibility will be based on reviews of medical records and echocardiographic results before baseline visits. After confirming study eligibility, baseline examinations (see the next section) will be conducted. Subsequently, patients will be randomized in a double-blind fashion to receive either udenafil or placebo (1:1) on top of any background therapeutic regimen in compliance with current recommendations [16], utilizing the randomization scheme depicted in Figure 2. An independent computer-generated list of random number will be used for participant allocations. Patients will receive either 50 mg udenafil or placebo twice daily for the first 4 weeks, and then if tolerated the dosage will be doubled to 100 mg twice daily for the next 8 weeks. Placebo and active study drugs (that is, udenafil) will appear to be identical and will be provided in blinded kits.

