### Safety

Any participants with a hypersensitivity reaction to the study drug or an adverse event after study medication, those that do not want to remain in the trial, or those that comply with medication <80% will be dropped from the trial, as will those judged to be at risk due to participation in the trial by an attending physician.

Udenafil has been reported to be safe and well tolerated by healthy volunteers [17], and by patients with erectile dysfunction [14]. No serious adverse events occurred in either study. Common adverse events included nausea, headache, facial flushing, febrile sensation, penile erection, and eyeball pain, all of which have been reported to adverse events of other PDE5 inhibitors. Adverse events will be immediately reported directly to the study investigators, and study staffs will be obligated to manage these events. Patients will be interviewed at each visit about the occurrence of any adverse events, and onset time, duration, and severity will be recorded on case report forms. The possibility of causal relationships between the study drug and the intensities of adverse events will be evaluated by the investigators. The investigators are mandated to report serious adverse events to the institutional review board within 24 hours of recognition. A data and safety monitoring committee will monitor the safety of patients participating in the trial and all ongoing serious adverse events will be closely followed until these conditions have stabilized.

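### The plan assumes that all lost primary outcomes are missing completely at random and omits them, yet its own removal rules create losses that plausibly depend on treatment or disease severity

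*Protocol article*

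**What the plan says.** All references are to the protocol article.

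- **Sample size calculation:** allows for 10% loss and characterises it thus: "data are missing completely at random, which implies that the missing data are unrelated to the study variables".
- **Statistical considerations:** declares an intention-to-treat principal analysis of all patients as randomised, then makes an exception: "data that are missing completely at random will be omitted without analysis". The primary comparison is an ANCOVA adjusted for baseline. No other rule for missing data is stated.
- **Safety:** patients leave the trial after a hypersensitivity reaction or an adverse event, if they no longer wish to take part, if compliance falls below 80%, and likewise "those judged to be at risk due to participation in the trial by an attending physician".
- **Study withdrawals:** patients may withdraw on request without giving a reason, and physicians may withdraw those for whom participation would be detrimental. Here the wording concerns leaving treatment, whereas Safety speaks of leaving the trial.
- **Follow-up protocol and Study endpoints:** the primary outcome has one post-baseline measurement, the week-12 exercise test.
- **Table 2:** all-cause death, cardiac death and admission for heart failure are secondary endpoints.

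**The concern.** MCAR means that the chance of a missing value has nothing to do with treatment, prognosis or outcome. Removal for adverse events, low compliance or judged risk is hard to square with that. The Safety section itself names known adverse effects of the drug class, so loss may differ by arm, and patients judged at risk may well be those with poor exercise capacity.

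A removed patient who is not tested at week 12 has no primary outcome, and under the stated handling leaves the analysis. If such patients would have had low values, the arm that loses more of them looks better than it is. The direction is not known in advance. Excess loss through intolerance would favour udenafil, and excess loss through deterioration on placebo would work against it. With 26 patients per arm, a few selective losses are enough to matter.

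**Working it through.** **1. The plan's own figure.** Inputs from Sample size calculation: expected week-12 values "14.0 ml/kg/minute in the placebo group and of 16.1 ml/kg/minute in the udenafil group", so the difference is 16.1 − 14.0 = 2.1; SD 2.5; 80% power; two-sided 5%.

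n = 2(1.960 + 0.842)² × 2.5² / 2.1² = 22.25, rounded up to 23 per group. This agrees with the text, which "will require 23 patients per group for a standard deviation of 2.5 ml/kg/minute". Inflating for loss, 23 / 0.9 = 25.6, rounded up to 26 per group or 52 in total. The arithmetic reproduces. The question is only the assumed mechanism and the omission.

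**2. The mechanism against the removal rules.**

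| Reason for loss | Where stated | Plausibly unrelated to treatment or severity? |
|---|---|---|
| Hypersensitivity or adverse event | Safety | No, can depend on treatment |
| Compliance below 80% | Safety | No, tolerability and illness both affect it |
| Judged at risk, or participation detrimental | Safety; Study withdrawals | No, reflects clinical state |
| Own wish | Safety; Study withdrawals | Possibly; reason need not be given |
| Death | Not a listed reason; endpoint in Table 2 | No, and it rules out the week-12 test |

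**3. Size without baseline adjustment.** If a fraction f of an arm is omitted and those patients would have scored D lower than completers, the completer mean is too high by f × D. The bias in the difference is (f₁ − f₀) × D. The documents give neither the split by arm nor D, so both are assumed. Overall loss is held at 10%.

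| Loss by arm | D | Bias | Share of 2.1 | Type I error |
|---|---|---|---|---|
| 10% / 10% | any, same in both arms | 0 | 0% | 5.0% |
| 15% / 5% | 1.25 | 0.125 | 6% | 5.3% |
| 15% / 5% | 2.5 | 0.25 | 12% | 6.4% |
| 15% / 5% | 5.0 | 0.50 | 24% | 10.5% |
| 20% / 0% | 2.5 | 0.50 | 24% | 10.4% |

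**4. Size under the planned ANCOVA.** Baseline adjustment removes part of the selection, so step 3 overstates the bias for this plan. Simulation: 26 per arm, no treatment effect, SD 2.5, assumed baseline to week-12 correlation 0.7. In each arm the patients lowest on a selection score are lost: 4 in one arm and 1 in the other (5 / 52 = 9.6%). The score's correlation with the week-12 value is set to 0.5 or 1.

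- Correlation 0.5: bias about 0.12 (0.12 / 2.1 = 6% of the planned effect), type I error about 6%.
- Correlation 1: bias about 0.28 (0.28 / 2.1 = 13%), type I error about 9.5%. A repeat run gave 0.27 and 9.7%.
- Loss of 3 v 3: bias zero to within simulation error at either correlation. At correlation 1 the rejection rate was still about 7%, because cutting the lower tail in both arms understates the residual variance. Part of the 9.5% is therefore not due to bias.

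**The case against.** - **The omission sentence covers only MCAR data, for which omission is harmless, and it is worded as an exception to the intention-to-treat statement.** As a literal reading this stands. The text does not say outright that every patient without a week-12 value is deleted, and it is not a flat self-contradiction. But the sample size section labels the entire expected loss MCAR, so in effect omission is the handling the article fixes.
- **Other missing data may be dealt with in the full protocol or analysis plan.** This also stands: the absence of a further rule is not the finding. The finding is that the article states a premise that its own removal rules contradict.
- **ANCOVA protects the comparison.** Partly. In the simulation above it cuts the bias roughly in half. It deals with loss that depends on baseline VO2, but not fully with loss caused by later adverse events or deterioration.
- **Patients lost to adverse events or poor compliance need not have low VO2, and loss may be balanced.** Correct. Neither the size nor the direction of bias can be derived from the documents.

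A reader might also infer that the protocol lists death and heart failure admission among its reasons for loss. It does not; both appear only as secondary endpoints. Death does make the week-12 test impossible, but admission is simply recorded at visits.

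**Conclusion.** The concern holds as a conflict between stated passages. The MCAR premise in Sample size calculation and the omission in Statistical considerations do not fit the removal rules in Safety and Study withdrawals, and omitting those patients weakens the declared intention-to-treat analysis.

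The likely distortion is modest: about 0.12 ml/kg/minute under moderate selection and about 0.28 under complete selection. This rests on a 4 v 1 split, a baseline correlation of 0.7 and the SD of 2.5, of which only the SD comes from the plan. A reader might infer from the unadjusted figures that bias near 0.5 is to be expected. The documents do not support that, because the planned analysis adjusts for baseline and the larger values need extreme splits or large deficits. Nor is the sample size arithmetic at fault. The point should be corrected before analysis, but it does not by itself invalidate the design.

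**What to change.** 1. Delete the MCAR premise from Sample size calculation and Statistical considerations. The 10% allowance can stay as a planning figure.
2. Reconcile the Safety wording (leaving the trial) with the Study withdrawals wording (leaving treatment) and with the intention-to-treat statement. State that week-12 VO2 from patients who stopped treatment enters the analysis wherever it was obtained.
3. Keep ANCOVA on all randomised patients, under an explicit missing-at-random assumption given arm, baseline VO2 and data already collected. If imputation is used, week-4 BNP and NYHA class are available. Reason for discontinuation should not be relied on: patients need not give one, and its effect cannot be estimated if no removed patient has a week-12 value.
4. Prespecify one sensitivity analysis that does not assume MCAR and also relaxes the missing-at-random assumption, since imputation alone does not address patients too ill to exercise. Options are a tipping-point (delta-adjusted) analysis, or worst rank for patients who died or could not exercise because of heart failure.

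The cost is revised wording, a little more programming and slightly wider intervals. No additional scheduled measurements are needed.

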## Discussion

Vasoconstriction is a pathophysiological hallmark of chronic HF, which involves the systemic and pulmonary circulations, and results in increased impedance of the left and the right ventricular ejection. Defective nitric oxide release is a major contributor to vasoconstriction in chronic HF [6]. The potentiation of nitric oxide signaling thus represents an interesting pharmacological approach. Furthermore, the inhibition of PDE5, the predominant isoenzyme that metabolizes cGMP [23], has attracted interest as a potential therapeutic tool in chronic SHF. Experiences accumulated in patients with pulmonary arterial hypertension provided the rationale for a therapeutic PDE5 inhibition in chronic SHF. Since the first description of the favorable effects of PDE5 inhibitors in pulmonary arterial hypertension [7], the positive effects of PDE5 inhibition on cardiac remodeling and secondary pulmonary hypertension have raised the possibility that chronic PDE5 inhibition offers a potential adjunct to the current pharmacological management of chronic SHF [10,22,24]. In addition, cGMP upregulation by PDE5 inhibition has also been reported to modulate the contractility of hypertrophied right ventricles [25].

Sildenafil was the first PDE5 inhibitor introduced to the clinical arena, and thus has been extensively investigated in experimental and clinical cardiology research sectors. Bocchi and colleagues evaluated the efficacy of sildenafil for the treatment of erectile dysfunction in patients with chronic SHF, and found that sildenafil improved exercise capacity [26]. Furthermore, in a study of 13 chronic SHF patients of New York Heart Association class III, Lewis and colleagues showed that sildenafil improves maximal V_O2_ and reduces V_E_/V_CO2_ slope [10]. As a result of these studies, PDE5 inhibitors are now considered good candidates for the treatment of chronic SHF.

Some PDE5 inhibitor brands can now be prescribed. However, although these PDE5 inhibitors are similar in terms of mode of action and molecular structures, their potencies, pulmonary vessel selectivities, and half-lives differ [27]. As a representative example, the onset of action of sildenafil is rapid, and as mentioned above its plasma half-life is 4 hours [28,29], which means that patients take the medication three times a day. In contrast, the plasma half-life of udenafil is 7 to 9 hours, and thus medications can be reduced to twice daily so patient compliance should improve [30] and eventually prognosis should benefit [31]. In this trial, the relatively short-term effects of udenafil on the exercise capacity of chronic SHF patients will be evaluated. Notwithstanding, we believe that this study will open a door to new therapeutic prospects for the long-acting PDE5 inhibitor, udenafil, and will help provide a new therapeutic option for chronic SHF patients.

The proposed ULTIMATE-SHF trial, as outlined above, will be a randomized, placebo-controlled, double-blind clinical trial designed to investigate the therapeutic effect of a new, long-acting PDE5 inhibitor, udenafil, in patients with chronic SHF. If an improvement in exercise capacity, as determined by peak V_O2_, is demonstrated, udenafil could become a valuable therapeutic auxiliary for patients with chronic SHF that receive maximal medical management for SHF based on the current guidelines [16].

## Trial status

Patient recruitment.

## Abbreviations

cGMP: Cyclic guanine monophosphate; CPET: Cardiopulmonary exercise test; HF: Heart failure; LV: Left ventricular; PDE5: Phosphodiesterase type 5; SHF: Systolic heart failure; VE: Minute ventilation (l/minute); VCO2: Carbon dioxide production (ml/kg/minute); VO2: Oxygen uptake (ml/kg/minute)
